### Interviews and focus groups

The interview component of the research study aims to collect in-depth qualitative data on individuals’ behaviours, attitudes and ecological characteristics, including exploring potentially more sensitive factors, such as the influence of family and peers. It is expected that the interviews will expand on the depth of survey findings, broadening the perspective of contextual factors and their influence on tobacco use [50,81]. The use of open ended questions will provide broader scope and more detailed and enriched qualitative data on the determinants of tobacco use, including both barriers and enablers to tobacco use [50,82]. As outlined in the *Synthesis: underpinning theories*, analysis of a range of data sources, data collection methods and the weight of evidence is expected to provide a more comprehensive view of tobacco use [50]. Thus, each form of data collection―survey; interviews; focus groups; and existing data collections―will independently provide part of the story for the research aim, objectives and research questions, but together, they will contribute to a higher level of analysis and a more comprehensive understanding of tobacco use of Indigenous Australians living in the ACT [50,81].

Objectives of the interview component include investigating and determining knowledge of the existence and content of the multi-component tobacco control strategy, and investigating and exploring in particular:

•smoking, quitting and non-smoking behaviours; and

•is there an association between various social determinants, such as education and employment, and being a smoker or non-smoker. This will include exploring social norms and the influence of social networks.

#### Sample size

The sample size of the interview component (and the focus group component) of this study is based on theoretical saturation. Thus, an exact sample size for the project can only be ascertained as the project progresses, as it will be based on the numbers required for the data to be rich and detailed enough to support thematic analysis. Theoretical saturation will be achieved through collecting data across a diverse range of participants to fully flesh out ideas and themes, until no new themes emerge [37,81,97,100]. Theoretical saturation also indicates the development of categories in relation to their properties and other characteristics, including variation [37,81]. It is anticipated that at a minimum, a sample of 25 participants will be required based on previous studies, such as the "Starting to Smoke" Experiences of Indigenous Youth study [101]. We will offer multiple days, times and locations to participate in the interviews, working with the community organisations and potential participants to ensure participation is as convenient as possible.

#### Analysis

In investigating the influence of social networks on smoking behaviours; the impact of tobacco control programs in the ACT on tobacco behaviours; and if there is an association between some social factors and being a smoker or non-smoker, we will follow some procedures and principles of grounded theory [100,102]. This is to ensure that we do not shift concepts into incongruent situations. Grounded theory involves grounding text in the context that it was constructed [100,102]. Grounded theory will form the underpinning conceptual framework that informs the analysis for the interview and focus group components of this research. The grounded theory approach will be modified as the research project is primarily descriptive in outcome, rather than theory generating. Grounded theory utilises a systematic, inductive research process to generate grounded theory that emerges through constant comparative analysis of qualitative data [37,103]. This "general method of comparative analysis" results in systemic theory, identifying core variables that are grounded in the collated and synthesised data; assisting to interpret the data [104], [105]. Glaser [104] explained that “grounded theory has the purpose of generating concepts and their relationships that explain, account for, and interpret the variation in behaviour (sic) in substantive area under study” [19,104]. Four fundamental criteria formed the basis for the methodology: fit, modifiability, relevance and work. *Fit (valid)*―grounded theory emerges from the analysis of data gathered from the system; therefore, the theory fits and is relevant. *Modifiability (control)*―grounded theory is induced from the interviews and associated documentation, thus, the theory closely reflects what is actually happening and is highly applicable [37,100,103]. *Relevance (understanding)*―as grounded theory fits and is relevant, it is readily understandable to the people interacting with the field because it portrays the latent patterns within the field [37,100,103]. *Work (generality)*―grounded theory fits the field, is relevant, and is understood by people within the field, it is important to understand that grounded theory produces theory, not description [37,100,103].

The research project is primarily descriptive in outcome, rather than theory generating and therefore, selected parts of the grounded theory process will be utilised during the research project. This modified grounded theory approach will include data collection through interviews and focus groups, which will be transcribed for coding, analysis and compilation of the findings [100]. Coding will include constant comparison, documentation and identification of themes throughout the findings, including core categories and sub-categories. The selective coding will also include constant comparison and documentation resulting in dense, saturated core categories. The core categories will be sorted, documented and described [37].

The interviews will follow an interview guide―informed by components of the National Aboriginal and Torres Strait Islander Social Survey, Health Survey and the National Drug Strategy Household Survey to address the research aim and objectives―to ensure methodological consistency. The interviews will be transcribed verbatim from electronic recordings. The transcripts will be coded using QSR Nvivo 10 and crosschecked with field notes. QSR Nvivo 10 will be utilised in coding each sentence according to meaning and content, supporting the thematic synthesis. As outlined in Figure 3, the text and codes will contribute to capturing the meaning and content of the interviews and each sentence. This will assist to identify similarities and differences, as abstract and analytical themes emerge, grouping the codes in a rational structure. The interview guide and the research objectives will also be utilised to group the sentences to ensure comprehensive analysis. This cyclical process will be repeated until no new themes emerge; adequately describing and explaining the aim and objectives of the research [37,103-106]. As outlined in Figure 4, the use of sentence coding will also assist to synthesize the qualitative research and recognise the concepts from individual interviews [37].

**Figure 3 F3:**
[figure not shown]
Network infrastructure.

**Figure 4 F4:**
[figure not shown]
Analysis process of interviews and focus groups.

### Focus groups

In complementing and expanding the other methods of data collection, the focus group component aims to generate more of a “real world” group dynamic with peers and to gain a combined local perspective from multiple viewpoints. This will help to explore the influence of social networks on smoking beliefs and behaviours and investigate if there is an association between some social factors and being a smoker or non-smoker. The use of focus groups can help generate new thinking and allow for a broader perspective of contextual factors in relation to the influences of tobacco use. As outlined, our research will utilise a number of data sources and analyses to enhance the validity of the prospective study, increasing the likelihood that the findings and interpretations will be credible and dependable [37,38,50,72]. Triangulation will strengthen our research and lead to a more comprehensive understanding of the complexity of tobacco use and tobacco control [37,50,91,107]. Thus, the objectives of the focus group component of the research run parallel to the other components of the research, further investigating and exploring in particular the influence of peers and social norms in relation to smoking behaviours.

#### Sample size

As with the interview component, the sample size of the focus group component of this study is based on theoretical saturation as previously outlined [37,97,100]. The focus group interviews will include a small group of participants, approximately 6 to 12 people of similar age, similar smoking habits or as deemed socially and culturally appropriate. For example: smokers, ex-smokers, non-smokers, men’s groups, ‘mums n bubs’ and youth groups. The focus group interviews will be approximately an hour in length and held at convenient locations for the participants, such as the participant’s office, clinic, the university or a nearby location.

#### Analysis

The analysis of the focus groups will align with the interview analysis, informed by the procedures and principles used in grounded theory to ensure that concepts are not shifted into incongruent situations [100,102]. The focus groups will follow a focus group guide to ensure methodological consistency. In investigating if social networks influence smoking beliefs and behaviours, if ACT tobacco control programs impact on tobacco behaviour and if there is an association between some social factors and being a smoker or non-smoker, we will follow some procedures and principles of grounded theory. Each focus group session will be transcribed verbatim from electronic recordings, with the transcripts coded using QSR Nvivo 10 and crosschecked with field notes. The text and codes will contribute to capturing the meaning and content of the focus groups, assisting to identify similarities and differences, as abstract and analytical themes emerge; grouping the codes in a logical structure. The focus group guide and the research objectives will also be utilised to group sentences and themes [37,103-106].

### Existing data collections

A number of existing data collections will also be used in our study. These data collections will assist in triangulation, complementarity and integration of the quantitative and qualitative data [50,78,82,108]. The pre-existing data collections are expected to include de-identified data collected from health organisations, including:

•Talking About the Smokes data―Talking About the Smokes is a national survey modelled on the International Tobaccciso Control Policy Evaluation Project to improve the understanding of smoking and quitting behaviours within the Indigenous Australian community [109]. The Project has been adapted to suit the context of smoking cessation and tobacco control for Indigenous Australians, and includes a data collection site within the ACT region [109];

•PBS items―the PBS is part of the Australian National Medicines Policy and provides affordable access to necessary medicines for Australians [110]. There are a number of nicotine replacement therapy (NRT) items listed on the PBS (NRT items – 3414Q, 5571 F, 5572G, 5573H) to assist smokers with nicotine withdrawals and to help smokers make a quit attempt [110]. The volume of NRT items accessed through the PBS can be monitored by jurisdiction, including within the ACT [110]; and

•Quitline call data―Quitline is a telephone services that aims to offer treatment and provide timely information that will help smokers make a quit attempt [111]. De-identified data could include call volume, call volume by post code and number of quit attempts.

#### Analysis

Analysis will incorporate descriptive statistics and comparisons between the pre- and post-intervention groups, including usage patterns of relevant PBS items and Quitline call volume. For example, post-intervention comparisons between the pre and post-intervention groups using chi-square and T-tests will be carried out. It would be expected that there would be increased uptake of NRT on the PBS post intervention and increased calls to Quitlines [81,99]. Analysis will include assessment of the means, ranges and rates to identify commonalities and disparities between this existing data collection and the primary data collected through the survey, interviews and focus groups. The available data from Talking About the Smokes will influence what sort of analysis can be undertaken. This will be explored in due course. Computations will be undertaken using SPSS and Microsoft Excel for statistical analysis [83-85].

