### Limitations

Whilst the ideal study design would be one that included a randomised ‘control’ group it is not practical or possible due to resource constraints to run such a study when the intervention is aimed at all Indigenous Australian people living in the ACT. In order to address some of these limitations, we propose using a mixed-methods approach that offers a range of perspectives on a program's processes and outcomes and a greater understanding of the findings.

Pre-test and post-test design are not as robust, but they are widely used and accepted in behavioural research for the purpose of comparing groups and/or measuring change resulting from experimental treatments or interventions.

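### Chi-square and t-tests on before/after PBS and Quitline volumes cannot separate the program from background trend or concurrent policy

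*Protocol article*

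**What the plan says.** Under Existing data collections, the Protocol article lists three sources: the Talking About the Smokes survey, PBS nicotine replacement items (four item codes) and Quitline calls. For the PBS it states: "The volume of NRT items accessed through the PBS can be monitored by jurisdiction, including within the ACT". For Quitline: "De-identified data could include call volume, call volume by post code and number of quit attempts".

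The Analysis subsection that follows plans descriptive statistics and comparisons between pre- and post-intervention groups, "including usage patterns of relevant PBS items and Quitline call volume". As an example it gives: "post-intervention comparisons between the pre and post-intervention groups using chi-square and T-tests will be carried out". The expected direction comes next: "It would be expected that there would be increased uptake of NRT on the PBS post intervention and increased calls to Quitlines". Means, ranges and rates are also to be assessed, to find agreement and disagreement with the primary data. Only the Talking About the Smokes analysis is left open until the available data are known.

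The Limitations section states that "the intervention is aimed at all Indigenous Australian people living in the ACT" and concedes that a randomised control group is not feasible. The Background section reports a long national fall in smoking, from about 34% in 1980 to 15% in 2010, and recently implemented plain packaging.

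**The concern.** There are two problems, and a third that depends on a fact the article does not give.

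- **Unit of analysis.** The survey has groups of respondents who can be compared by chi-square or t-test. The PBS and Quitline sources, as described, have none: each is a count per period for an area. The survey's form of comparison has been carried over to data of another kind.
- **Trend and concurrent policy.** A difference between two period averages combines the program with everything else that changed over the same time. The subsection names no trend adjustment, baseline series or comparison jurisdiction.
- **Population.** The program is aimed at Indigenous people in the ACT, while the PBS "provides affordable access to necessary medicines for Australians". No restriction to Indigenous users is stated for either source, and nothing says that one is impossible.

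These series are there for triangulation, and the Limitations section relies on mixed methods to offset the missing control group. A strand that moves with background trend can appear to support or contradict the survey for reasons unrelated to the program.

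**Working it through.** The article gives no volume, series length or error rate for this comparison, so there is no figure of its own to reproduce. The check asks how often the named tests reject when the program does nothing.

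**Assumed inputs.** Monthly Poisson counts; 12 months before and 12 after; starting volume B = 50 or 300 a month; steady growth g = 0.25%, 0.5% or 1% a month; two-sided 5% level. The roughly 12 months under Aim and objectives is the gap between survey waves, so even the series length is an assumption.

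**Step 1: size of the spurious difference.** With smooth growth, the ratio of post-period to pre-period total is (1+g)^12:
- 1.0025^12 = 1.030
- 1.005^12 = 1.062
- 1.01^12 = 1.127

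The post-period is therefore 3%, 6% or 13% higher with no program effect.

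**Step 2: chi-square on the two period totals.** With expected totals a (pre) and b (post), the statistic is (a−b)²/(a+b), and its signed root is centred near (b−a)/√(a+b). For B = 50 and g = 0.5%, a = 616.8 and b = 654.8, so 38.0/√1271.6 = 1.07. The rejection probability is about P(Z > 1.96 − 1.07) = 19%. At B = 300 the root is √6 times larger, 2.61, which gives about 74%.

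**Step 3: t-test on monthly counts, by simulation.**

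| Growth per month | t-test, 50 a month | t-test, 300 a month |
|---|---|---|
| 0 | 5% | 5% |
| 0.25% | 8% | 23% |
| 0.5% | 17% | 67% |
| 1% | 52% | over 99% |

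**Step 4: serial correlation alone.** With no trend but month-to-month correlation of 0.3 or 0.5, the t-test rejects in 14% or 24% of runs.

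**Step 5: falling background.** At −0.5% a month the ratio is 0.995^12 = 0.942. A real 6% program rise would give 1.06 × 0.942 = 0.998, so no visible change. A false significant increase almost never occurs in this case; the error is masking.

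**Step 6: trend adjustment.** A segmented regression (level change adjusted for linear trend), run with no program effect, volumes of 50 to 300 a month and growth of 0 to 20% a year, rejects in 4.7% to 5.4% of runs. This removes smooth trend only. A national policy change that coincides with the program still needs a comparison series.

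**Step 7: dilution, only if records cannot be limited to Indigenous users.** The overall rise equals the Indigenous share of volume times the rise in that group. For an assumed share of 2% to 20% and a true 30% rise, the total moves by 0.02 × 30% = 0.6% to 0.20 × 30% = 6.0%. A rise of 0.6% (0.6/0.98) to 7.5% (6.0/0.80) among other users alone would give the same total.

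**The case against.** The strongest reply has five parts.

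- **The tests are only an example, and secondary analyses are often detailed elsewhere.** This stands in part. However, the article does name tests for these volumes and offers no suitable method beside them; only the Talking About the Smokes analysis is deferred. That source is a survey of people, so chi-square and t-tests can be proper there.
- **No text says that a rise will be credited to the program.** Correct. A reader might infer that from the before/after framing and the stated expectation, but an expected direction is an ordinary hypothesis, and the stated purpose is triangulation. The defect is that the comparison cannot distinguish the explanations, not that a misattribution has been announced.
- **Whole-ACT data are not stated.** Also correct. A reader might infer that the volumes cover all ACT residents and that most users are non-Indigenous. The article does not give eligibility for the four item codes, says only what Quitline data could include, and does not say whether Indigenous status is recorded. Dilution is therefore conditional.
- **The false-positive rates depend on assumptions.** They do: at 50 a month they are far lower than at 300, and the article gives no trend for nicotine replacement or calls. Season is not an added problem if two full 12-month blocks are compared, since both cover the same calendar months.
- **The design limit is disclosed.** The Limitations section accepts that "the ideal study design would be one that included a randomised ‘control’ group it is not practical or possible" and that pre/post designs are less robust. It does not address trend in these series, and its only remedy is the mixed-methods approach of which they are part.

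**Conclusion.** The point holds for the unit of analysis and for trend. Chi-square and t-tests on aggregate PBS and Quitline counts cannot tell a program effect from background drift or concurrent national policy. Under the assumed upward trends and 12 + 12 months, the false rejection rate of the t-test runs from about 8% to 52% at 50 items a month and from 23% to over 99% at 300, against a nominal 5%. A downward trend would mask an effect instead. The direction of the real error is unknown, because the article gives neither volumes nor trends.

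Dilution by non-Indigenous use is an added risk only if the records cannot be limited to Indigenous users. The documents do not support asserting that it will occur, nor that the plan commits to reading a rise as program effect. The weakness affects a supporting strand of the evaluation, not the survey comparison on which the sample size is based.

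**What to change.** For the PBS and Quitline volumes, replace the chi-square and t-tests with a trend-adjusted Poisson or negative binomial model of monthly counts that allows for serial correlation. Ask the custodians for as long a pre-period as they can supply and for the same series from at least one other jurisdiction, to serve as comparison. State whether Indigenous-identified items or calls are available and restrict to them where they are. If the longer series, the comparison jurisdiction or the identified records cannot be had, report the volumes descriptively as context and say that they are not evidence of program effect. The tests can stay for person-level survey data such as Talking About the Smokes.

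The cost is a slightly wider data request and a standard model; recruitment, survey and program are untouched. There are real downsides. With only about 12 points on each side, trend and serial correlation are poorly estimated, so the program estimate will be imprecise, and these sources will support a weaker conclusion than the present wording suggests.

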### Ethical review

The project has been informed by and is in compliance with the World Medical Association Declaration of Helsinki, the National Statement on Ethical Conduct in Human Research, Values and Ethics - Guidelines for Ethical Conduct in Aboriginal and Torres Strait Islander Health Research and Guidelines for Ethical Research in Australian Indigenous Studies [112-114]. The project takes into account the sensitivities around sampling Indigenous Australian people aged 12 years of age and older. A key ethical component and integral facet of the study is community engagement. In engaging with the community, we are also partnering with Winnunga Nimmityjah Aboriginal Health Service, a community controlled health organisation and working with other community stakeholders in the area. The research received ethics approval from the University of Canberra Human Research Ethics Committee (Project number 12163) and the ACT Health Human Research Ethics Committee (ETH10.12.232).

## Discussion

There is a challenge ahead if we are to achieve the ambitious ‘Close the Gap’ Campaign for Indigenous Health Equality target, to close the health and life expectancy gaps between Indigenous Australians and non-Indigenous Australians within a generation (2031) [47,115] and to halve the 2009 smoking rate of Indigenous Australian people by 2018 [42]. It is expected that this research will have benefits for the Indigenous Australian health sector and the community in terms of adding to the evidence for what might influence smoking behaviour and to help inform future tobacco control interventions.

Our understanding of attitudes, behaviours and effective tobacco control and the influence of how social networks influence smoking in Indigenous Australian communities is very limited. Social networks are theorised to significantly influence behaviour change processes. Through this project, we expect to contribute new knowledge about factors influencing tobacco use among the Indigenous Australian community.

